### Study products

The test product is a food for special medical purposes in powder form, used as a complement to the regular hospital feeding regimes of preterm infants. The product will be packaged into two separate sachets: Part A, containing *B. breve* M-16V, and Part B, containing prebiotic oligosaccharides scGOS and lcFOS in a ratio of 9:1, as well as L-glutamine. The control product will be similarly packaged into two separate sachets as follows: Part A, containing maltodextrin, and Part B, containing maltodextrin and casein and whey protein hydrolysates.

The study products will be provided to the study sites by Danone Nutricia Research and manufactured according to good manufacturing practice*.*

### Supplementation

Study product supplementation will start between 48 and 72 h after birth or, if the infant is clinically unstable as soon as possible thereafter, and will continue until 36 weeks postmenstrual age. If the infant is discharged home or fully breastfed before 36 weeks postmenstrual age supplementation will be stopped. Study product Part A will be administered enterally once per day as a single daily dose not supplemented to feeding or medication. The dosage of *B. breve* will depend on birth weight: Infants with a birth weight ≥ 1000 g will receive 3 × 10^9^ colony-forming units (cfu) per day; Infants with a birth weight < 1000 g will receive 1.5 × 10^9^ cfu per day, to be increased to 3 × 10^9^ cfu per day when they have reached enteral feeding intakes of 50 ml/kg/day. Study product Part B will be administered enterally supplemented to the regular milk feed (breast milk or preterm formula, depending on parents’ choice). Dosage will be increased in a stepwise fashion. Based on the infant’s weight, daily intake of enteral feeding and the desired (maximum) osmolarity of the feeding, a supplementation schema was created, starting with a minimum dosage of 0.05 g/day L-glutamine and 0.1 g/day scGOS/lcFOS and aiming for a final dose of 0.3 g/kg/day L-glutamine and 0.6 g/kg/day scGOS/lcFOS when the infant receives full enteral feeding (120 ml/kg/day for 1 day). The final dosages of L-glutamine and scGOS/lcFOS were based on the GEEF study [45] and CARROT study [51], respectively, in which supplementation was well tolerated.

### Outcome measures

#### Primary outcome

The primary outcome parameter in this study is integrity of white matter tracts throughout the brain, measured as FA assessed with DTI magnetic resonance imaging (MRI) at TEA. DTI detects the direction of diffusion of water molecules, which is influenced by the process of increasing myelination. Many studies have shown that FA - a measure of degree of diffusion in one direction - and tractography - a reconstruction of tracts using FA - are predictive of long-term neurodevelopmental outcome [52]. DTI images will be analysed using Tract-Based Spatial Statistics (TBSS), [53] part of the FMRIB Software Library [54]. TBSS is a voxelwise statistical method in which all infants FA data will be projected onto a mean FA tract skeleton and will be cross-subject analysed. TBSS analysis is sensitive as an imaging biomarker in the preterm population, [55] and can be used as a suitable biomarker of disease and treatment effects in children born very preterm [52, 55, 56].

#### Secondary outcomes

White matter injury, measured with the white matter injury score according to Kidokoro et al., [57] which evaluates cystic lesions, focal signal abnormality, myelination delay, thinning of the corpus callosum, dilated lateral ventricles and volume reduction on T2- and T1-weighted MR images acquired at TEA.Brain tissue volumes (cerebellum, cortical grey matter, unmyelinated white matter, deep nuclear grey matter, ventricular volumes and extracerebral cerebrospinal fluid) and cortical morphology (sulcation index, cortical surface area and cortical thickness) assessed using the segmentation method of Moeskops et al. [58] of T2- and T1-weighted MR images made at TEA.The occurrence of serious neonatal infections (defined as culture proven or clinical sepsis with associated clinical symptoms; clinically significant NEC [i.e., Bell’s stage two or higher]; meningitis with or without positive culture; or pneumonia [positive culture of tracheal aspirate, bronchial secretion, or sputum positive for microorganisms with associated clinical symptoms]) [45, 51] until TEA.Serum concentrations of specific circulating inflammatory markers such as IL-6, IL-10, TNF-α and IL-8/CXCL8 measured with flow cytometry and Luminex at 7, 21 and 42 days postnatal, 30 and 36 weeks postmenstrual age, discharge to other hospital and TEA (optional, in a subgroup).Motor and cognitive development assessed with the Bayley Scales of Infant and Toddler Development, Third Edition, [59] at 24 months corrected age.

#### Safety outcomes

The following parameters will be assessed to evaluate safety of supplementation with the study product:
Occurrence, type and duration of (Serious) Adverse Events.Adequate growth for weight (g/kg/week), length (cm/week) and head circumference (cm/week) until the end of intervention.Growth velocity and anthropometric z-scores until 24 months corrected age.Number of days of parenteral nutrition.Time in days to achieve full enteral nutrition (defined as 120 ml/kg/day for 1 day).Feeding tolerance (frequency and daily volume of gastric residuals, the occurrence of diarrhoea and constipation and stool frequency).Serum glutamine and glutamate concentrations (optional, in a subgroup).

### Study assessments

Table 2 (see Additional file 1) shows a timeline of all assessments for each infant.

### Data collection

All study data will be collected in a validated eCRF (VIEDOC, from Pharma Consulting Group during the intervention period; Castor during the follow up period). To guarantee data quality only trained study staff can enter data in the eCRF. Data will be collected and stored in line with data privacy laws, and details on data management are documented in the data management plan. Collected data will include: gender, GA, (birth) weight, (birth) length, (birth) head circumference, parental level of education, parental head circumference, score for Neonatal Acute Physiology – Perinatal Extension (SNAPPE-II), obstetric and perinatal details (such as presence of chorioamnionitis, prenatal medication, relevant maternal illnesses, Apgar scores and cord blood parameters), neonatal morbidity (such as infant respiratory distress syndrome, need for respiratory support, neonatal infections, patent ductus arteriosus, intraventricular haemorrhage and post haemorrhagic ventricular dilatation), neonatal medication, enteral and parenteral feeding characteristics and cumulative intake. Additionally stool samples will be collected at fixed time points to evaluate bacterial colonisation and the development of the microbiome and to be able to detect possible cross contamination with *B. breve* M-16V in infants allocated to the control group, using *B. breve* M-16V specific primers.

### Protocol compliance and missing data

Study product preparation and supplementation will be recorded in a log and the infant’s medical file and is therefore traceable. All study procedures will take place during the regular hospital admission or regular follow up. Only the MRI in a subgroup of infants (infants born between 28 + 0 and < 30 + 0 weeks GA with a birth weight ≥ 1000 g and with no significant abnormalities on serial cranial ultrasound images) will be specifically performed for study purposes, which will be clearly communicated with parents before informed consent is given. This will likely minimise non-compliance and missing data since the percentage of infants attending regular follow up in our hospital is very high (> 90%).

### Safety reporting

During the entire study period from first intake of study product until last follow up visit data on safety (i.e., Adverse Events and Serious Adverse Events) will be collected. An overview of Serious Adverse Events will be presented to the ethics committee regularly.

An independent Data Monitoring Committee (DMC) has been established to perform safety surveillance and to protect the scientific validity and credibility of the study. The DMC will make recommendations regarding safety and/or tolerance parameters and/or modifications in protocol based on the results of the safety evaluation, interim analyses and emerging evidence from other studies and/or relevant other sources of evidence. The DMC may also give the recommendation on continuation, termination or continuation with modifications for the study. The activities and responsibilities of the DMC have been planned following the recommendations of the DAMOCLES study related to the DMC members [60].

Two interim analyses will be performed by an independent statistician: one when 20 infants have completed the study until TEA and another when 40 infants evaluable for the interim analysis have completed the study until TEA. The objectives of the interim analyses are to evaluate safety and/or tolerance outcomes. Data for safety evaluation purposes and the interim analyses results will be supplied in strict confidence to the DMC. The safety evaluation and interim analyses will be conducted on semi-blinded data (“X” and “Y”). At all times the DMC has the right to decide to fully unblind the study groups or to unblind the treatment for one specific infant (e.g., in case of sepsis). As unique randomisation numbers will be used unblinding an individual infant will not lead to unblinding of others. In case of a clinically relevant (to be judged by the DMC) difference in death, sepsis, meningitis or NEC between the test group and control groups the DMC can recommend termination of the study. Unless decided otherwise by the DMC the study will be stopped if an infant is diagnosed with sepsis (a Serious Adverse Event) and *B. breve* M-16V is subsequently detected in the infant’s blood. In addition the DMC can recommend termination of the study for other reasons.

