### Treatment allocation and blinding

After eligibility has been assessed and informed consent has been obtained the infant will be enrolled in the study. To randomise an infant to the study, investigators will log in to the electronic Case Report Form (eCRF) and follow the prompts to input infant data. Only investigators specifically trained to perform randomisation will have access to the eCRF. Based on the order in which infants enter the study and stratified by sex, the infant will be assigned a randomisation number by the eCRF system. The infant will receive the product with the code corresponding to his/her randomisation number. Twins and multiple births will be allocated to the same study group. Investigators, all site staff including medical and nursing staff and supporting staff who prepare the infant feedings, and parents will be unaware of treatment allocation.

The randomisation sequence will be generated using the PLAN procedure of SAS statistical software (Enterprise Guide version 4.3 or higher) by a statistician from Danone Nutricia Research who has no further involvement in the conduct of the trial. The permuted block randomisation will be stratified by sex (boys, girls) with a 1:1 allocation ratio of test and control product. The block size or sizes and whether the block size(s) will be fixed or randomly varied will be decided by and known only to the statistician. The packaging of the test and control products will be identical in appearance. The study product for each infant will be labelled using a unique random number according to the randomisation schedule. These random numbers will have been linked (via a code) beforehand to either test or control product. Which numbers correspond to which treatment will only be known to the supplies manager at Danone Nutricia Research.

The randomisation code will be broken after analysis of the primary outcome and other outcomes collected until TEA. Assessors, parents, hospital staff and all those involved in the conduct and/or decision making of the follow-up phase will remain blinded to study product allocation until follow-up database lock after the last infant has completed the study (24 months corrected age). In the case of a medical emergency that requires preliminary unblinding of study product, unblinding in the eCRF or with sealed unblinding envelopes stored at the UMC Utrecht will be possible.

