### Sample size calculation

The sample size needed for TBSS analyses has been estimated based on previous simulations of the sensitivity of TBSS for detecting treatment effects, as reported by Ball et al., who recruited infants with GA < 36 weeks who underwent successful DTI at TEA (baseline characteristics: median GA [range] 28 + 6 [23 + 4–35 + 2], median birthweight [range] 1130 g [630–3710 g]) [55]. The likelihood of TBSS detecting an effect of the intervention on the FA will depend on the overall FA increase and its distribution around the mean FA increase. The effect of the current intervention on FA is unknown. We hypothesize that the increase in FA in the intervention group will be moderate, in the order of 5%. TBSS analyses the relation between different parameters (e.g., GA, sex, intervention group) and the FA of voxels of the white matter skeleton (i.e., the inter-subject aligned centre of white matter tracts). Based on the simulations in neonates reported by Ball et al., in order to detect an estimated increase in FA of 5% in approximately 50% of the TBSS skeletal voxels 35 infants per intervention group are required [55]. They showed that TBSS can detect clinically relevant global differences in FA, even in small groups and can therefore be used as a powerful biomarker of white matter development [55]. In a recent study comparing the effects of high vs. lower breast milk exposure in 20 vs. 27 preterm infants group wise differences in brain connectivity at TEA were shown with TBSS [61]. Based on these results we assume this whole-brain DTI analysis technique is sensitive to the effects of our intervention with 35 evaluable infants per intervention group. In total 70 evaluable infants will be needed. To account for potential drop-outs and non-evaluable infants, the target population should consist of 88 randomised infants. This number includes allocated twins/multiple births.

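### Unblinding one twin or multiple also reveals the arm of its co-enrolled siblings, contrary to what the protocol states

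*Protocol article*

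**What the plan says.** All references are to the protocol article.

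- **Safety reporting.** The DMC may unblind the groups fully, or may "unblind the treatment for one specific infant (e.g., in case of sepsis"). The next sentence gives a reassurance and a reason for it: "As unique randomisation numbers will be used unblinding an individual infant will not lead to unblinding of others". It makes no exception.
- **Treatment allocation and blinding, siblings.** "Twins and multiple births will be allocated to the same study group". This rule has no exception either.
- **Treatment allocation and blinding, labelling.** "The study product for each infant will be labelled using a unique random number according to the randomisation schedule". This is the feature on which the reassurance rests.
- **Treatment allocation and blinding, emergencies.** There is a second route to individual unblinding, for an emergency in which an infant's code has to be opened early: "unblinding in the eCRF or with sealed unblinding envelopes stored at the UMC Utrecht will be possible".
- **Treatment allocation and blinding, who stays blinded.** Investigators, site staff "and parents will be unaware of treatment allocation". Those involved in follow-up stay blinded until the follow-up database is locked, after the last infant has reached 24 months corrected age.
- **Sample size calculation.** Multiples are in the trial. Of the 88 to be randomised the section says: "This number includes allocated twins/multiple births".

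**The concern.** A unique number per infant means that opening one code tells the reader nothing about an unrelated infant's code. It cannot do the same for siblings, because their link is the allocation rule and not the label. For them the property claimed in Safety reporting is one that the design does not have.

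If the sentence is taken at face value, a sibling whose arm has become inferable could go on being counted as blinded. That sibling may be in the same unit and under the same staff, and follow-up runs to 24 months corrected age. Several outcomes collected over that time involve judgement: clinical sepsis within the serious neonatal infection outcome, adverse event reporting, feeding tolerance and the Bayley assessment. The protocol's own example of a reason to unblind is sepsis. The Discussion puts late-onset sepsis at about 27% among infants of 1000 g or less at this centre, so the triggering illness is not rare, although nothing suggests that most cases would lead to unblinding.

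**Working it through.** The check is mainly logical. The plan states no figure on this point, so there is none to reproduce.

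**Step 1: the two rules together**

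| Relation to the unblinded infant | What links the two allocations | Probability that the second infant's arm is the revealed arm |
|---|---|---|
| Infant of another pregnancy | Separate number, 1:1 allocation | About 0.5 |
| Co-enrolled sibling | Same-group rule | 1 |

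The first row is what the sentence in Safety reporting describes. The second row contradicts it. Unique labelling leaves the second row unchanged, since each sibling has its own number and both numbers point to the same arm.

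**Step 2: who gains the information**

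The sibling is unblinded only to a person who (a) learns the first infant's allocation and (b) knows the same-group rule.

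- DMC route: if disclosure stays within the committee, bedside staff, parents and follow-up assessors do not meet condition (a).
- Emergency route: the code is opened in the eCRF or from an envelope held at the centre. Site staff may then meet (a). The investigators trained to randomise infants can be expected to meet (b), because they have to apply the rule.

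**Step 3: size per event**

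Inputs: 88 randomised and 70 evaluable (Sample size calculation). The first infant is unblinded in any case, so the cost of the sibling link in a twin pair is one additional infant.

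- Of those randomised: 1/88 = 1.1%. This is the more suitable denominator for infection and adverse event outcomes.
- Of those evaluable: 1/70 = 1.4%.

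A triplet set with all three enrolled would add two infants per event: 2/88 = 2.3%, or 2/70 = 2.9%.

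**Step 4: how often (assumption only)**

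The article does not give the share of infants from multiple births. Let that share be m, assume that all siblings are enrolled, and take an unblinded infant at random. One event then reveals at least one sibling with probability m. For k events, treated as independent, the probability of at least one exposed sibling is 1 − (1 − m)^k.

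| m (assumed) | Infants in sibling sets, 88 × m | k = 1 | k = 3 | k = 5 |
|---|---|---|---|---|
| 0.10 | 8.8 | 0.10 | 0.27 | 0.41 |
| 0.20 | 17.6 | 0.20 | 0.49 | 0.67 |
| 0.30 | 26.4 | 0.30 | 0.66 | 0.83 |
| 0.40 | 35.2 | 0.40 | 0.78 | 0.92 |

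The article does not give k either. The table shows only how the risk would scale. The contradiction in Step 1 depends on neither m nor k.

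**The case against.** The best defence reads the sentence in its setting. It stands in the DMC paragraph, where safety data are supplied in confidence, and it explains a coding mechanism: with individual numbers, opening one code does not open a whole arm, as a shared product code would. For unrelated infants that is correct, and a disclosure that stays with the DMC does not reach those who care for or assess the sibling. This stands as a limit on the consequences. It does not make the sentence true for siblings, because the sentence has no qualifier and the emergency route opens the same individual codes.

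A second defence is that a journal article need not set out who receives a code or how unblinding is recorded. That also stands: the absence of sibling procedures is not the point here, and the full protocol or DMC charter may contain them. The point is a sentence that is wrong as printed, which further detail elsewhere would not correct.

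Several stronger readings are tempting but are not supported:

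- *That the protocol justifies individual unblinding by this sentence.* The DMC's right is granted at all times, and the emergency route rests on the emergency. The sentence only comments on the consequences.
- *That parents and all staff know the same-group rule.* The article does not say that they are told it, though parents of twins could come to learn it.
- *That the database would record the sibling as blinded.* The article does not describe how unblinding is recorded.
- *That every multiple in the trial has lost its blind, or that a twin event costs two infants.* Loss needs an actual unblinding event, and the first infant of the pair is unblinded regardless of the sibling link.
- *That the primary result is at risk.* Fractional anisotropy from a voxelwise image analysis is little exposed as long as the image analysts are not told.

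**Conclusion.** The statement that individual unblinding leaves all other infants blinded is false for co-enrolled twins and multiples. This follows from the protocol article alone and needs no outside figure. The reach is limited. The statement holds for singletons and across pregnancies, and the problem matters chiefly when a code is opened at the site rather than within the DMC. It then touches the secondary and safety outcomes that involve judgement more than the primary outcome. Each twin event adds one infant, 1.1% of 88 or 1.4% of 70. The total effect cannot be stated, because neither the share of multiples nor the frequency of unblinding is given, and the 10% to 40% range used above is an assumption. The error is worth correcting because the correction is nearly free, and because a record of who was truly blinded is hard to rebuild afterwards.

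**What to change.** 1. In Safety reporting, limit the sentence to infants of other pregnancies, and add that unblinding one infant of a multiple birth reveals the arm of its co-enrolled siblings.
2. State, for both the DMC and the emergency route, that the code is released only to those who need it.
3. Record co-enrolled siblings in the eCRF as unblinded from the date of the event, so that they are counted as such when blinding is reported.

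The cost is a short text amendment and one eCRF flag. Same-arm allocation of siblings, the right to unblind, the sample size and the primary analysis all stay as they are.

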### Sample size calculation

The sample size needed for TBSS analyses has been estimated based on previous simulations of the sensitivity of TBSS for detecting treatment effects, as reported by Ball et al., who recruited infants with GA < 36 weeks who underwent successful DTI at TEA (baseline characteristics: median GA [range] 28 + 6 [23 + 4–35 + 2], median birthweight [range] 1130 g [630–3710 g]) [55]. The likelihood of TBSS detecting an effect of the intervention on the FA will depend on the overall FA increase and its distribution around the mean FA increase. The effect of the current intervention on FA is unknown. We hypothesize that the increase in FA in the intervention group will be moderate, in the order of 5%. TBSS analyses the relation between different parameters (e.g., GA, sex, intervention group) and the FA of voxels of the white matter skeleton (i.e., the inter-subject aligned centre of white matter tracts). Based on the simulations in neonates reported by Ball et al., in order to detect an estimated increase in FA of 5% in approximately 50% of the TBSS skeletal voxels 35 infants per intervention group are required [55]. They showed that TBSS can detect clinically relevant global differences in FA, even in small groups and can therefore be used as a powerful biomarker of white matter development [55]. In a recent study comparing the effects of high vs. lower breast milk exposure in 20 vs. 27 preterm infants group wise differences in brain connectivity at TEA were shown with TBSS [61]. Based on these results we assume this whole-brain DTI analysis technique is sensitive to the effects of our intervention with 35 evaluable infants per intervention group. In total 70 evaluable infants will be needed. To account for potential drop-outs and non-evaluable infants, the target population should consist of 88 randomised infants. This number includes allocated twins/multiple births.

